## Abstract

**Background:**

Women who are diagnosed with gestational diabetes mellitus (GDM) are at increased risk for developing prediabetes and type 2 diabetes mellitus (T2DM). To date, there have been few interdisciplinary interventions that target predominantly ethnic minority low-income women diagnosed with GDM. This paper describes the rationale, design and methodology of a 2-year, randomized, controlled study being conducted in North Carolina.

**Methods/Design:**

Using a two-group, repeated measures, experimental design, we will test a 14- week intensive intervention on the benefits of breastfeeding, understanding gestational diabetes and risk of progression to prediabetes and T2DM, nutrition and exercise education, coping skills training, physical activity (Phase I), educational and motivational text messaging and 3 months of continued monthly contact (Phase II). A total of 100 African American, non-Hispanic white, and bilingual Hispanic women between 22–36 weeks of pregnancy who are diagnosed with GDM and their infants will be randomized to either the experimental group or the wait-listed control group. The first aim of the study is to determine the feasibility of the intervention. The second aim of study is to test the effects of the intervention on maternal outcomes from baseline (22–36 weeks pregnant) to 10 months postpartum. Primary maternal outcomes will include fasting blood glucose and weight (BMI) from baseline to 10 months postpartum. Secondary maternal outcomes will include clinical, adiposity, health behaviors and self-efficacy outcomes from baseline to 10 months postpartum. The third aim of the study is to quantify the effects of the intervention on infant feeding and growth. Infant outcomes will include weight status and breastfeeding from birth through 10 months of age. Data analysis will include general linear mixed-effects models. Safety endpoints include adverse event reporting.

**Discussion:**

Findings from this trial may lead to an effective intervention to assist women diagnosed with GDM to improve maternal glucose homeostasis and weight as well as stabilize infant growth trajectory, reducing the burden of metabolic disease across two generations.

**Trial registration:**

NCT01809431

## Background

Pregnancy is an unrealized window of opportunity for primary prevention of diabetes. Approximately a third of women diagnosed with type 2 diabetes (T2DM) have a history of gestational diabetes mellitus (GDM), defined as carbohydrate intolerance during pregnancy [1,2]. GDM affects 1 in 20 pregnant women in the U.S. [1,2]. These women are at increased risk of developing GDM in subsequent pregnancies and of developing T2DM later in life [1,3-5], with a cumulative incidence as high as 70% [6]. Infants born to women with GDM have a 2-fold risk of developing obesity [7] and a greater risk of developing T2DM than infants born to normoglycemic women [8,9]. There is strong evidence that lifestyle interventions can reduce the risk of progression to T2DM by 58% in the general population [6,10-12] and by 55% among women with a history of GDM [6]. The American College of Obstetricians and Gynecologists [13] and the American Diabetes Association [1,2] recommend that women with GDM be counseled about diet, exercise, and weight reduction. However, several studies suggest that the advice is insufficient to change maternal behavior [14-16]. Effective interventions are therefore needed to improve health-promoting behaviors among women with a history of GDM. One-on-one lifestyle interventions such as the Diabetes Prevention Program are costly and did not target pregnant women [17]. However, group interventions have been found to be both acceptable and effective in promoting positive pregnancy behaviors [18,19]. Studies of women with GDM have found self-efficacy to be one of the few modifiable predictors of physical activity [20-22]. A recent study demonstrated that breastfeeding may reduce risk of progression to metabolic syndrome by as much as 86% by utilizing from 400 to 600 calories a day and stabilizing blood sugar [23].

It is imperative that women diagnosed with GDM decrease their BMI to < 25 kg/m2 after the birth of their infant, both to improve metabolic outcomes and to decrease progression to T2DM later in life [1,2]. Among reproductive aged women, excessive gestational weight gain is a consistent predictor of worsening obesity [24,25]. A total of 40% of normal weight women and 60% of overweight women exceed the Institute of Medicine (IOM) prenatal weight gain guidelines [26,27]. Compared with women who gain within recommended ranges, women who gain excessively are more likely to be overweight or obese 10 or more years later [24,28].

These risks are magnified among women with GDM, because those who are overweight or obese and do not lose weight postpartum are at increased risk for developing prediabetes, T2DM, hypertension, hypercholesterolemia and cardiovascular disease later in life [1,2]. The estimated total economic cost of diagnosed diabetes in 2012 was $245 billion, a 41% increase from the previous estimate of $174 billion (in 2007 dollars) [29].

To reduce the risk of progression to T2DM, interventions must counter secular trends in diet and physical activity. Nutritional quality has declined with an increased intake of sugared beverages and high calorie and high fat foods [27,30,31]. Less than 50% of adults currently eat five to six servings of vegetables per day [30,32]. Fast food intake has increased along with increased caloric intake and increased weight in adults [33].

Physical activity has decreased and sedentary behavior has increased both among in adults in the general population and among pregnant women [34]. Current physical activity guidelines for prenatal and postpartum women is 30 minutes on most if not all days of the week [35]. Approximately 75% of pregnant women do not meet the recommended levels of daily physical activity [36].

The intervention to be tested in our trial includes a comprehensive group **N**utrition and **E**xercise Education, Coping **S**kills **T**raining (**NEST**), and exercise intervention [37-39]. During pregnancy, participants receive a prenatal session on the benefits of breastfeeding for metabolic control and infant health [40-46]. At 6 weeks postpartum, they receive a session on diabetes education, and messages are reinforced with weekly educational and motivational text messages from the time of enrollment to completion of participant’s time in the study.

### Theoretical framework for the intervention

The study intervention is based on social cognitive theory [47-50], which posits that learning and practicing a new behavior enhances self-efficacy. When self-efficacy is enhanced, the probability that the new behavior will be maintained increases [47,48,50]. When an individual cannot effectively solve a problem, their confidence for dealing with the next problem is decreased [47-50]. Coping skills training assists mothers in dealing with problems they encounter as they incorporate new nutrition and exercise behaviors [47-50]. Our hypothesis is that cognitive-affective processes [51] will improve in women who receive breastfeeding, diabetes, nutrition and exercise education, coping skills training, exercise, a home-based exercise program, and weekly educational and motivational text messages. We further hypothesize that these women will increase self-efficacy, improve their nutrition and exercise behaviors, and manage their weight. These behavior changes, in turn, will decrease their risk of progression to T2DM and improve their infants’ outcomes [37-39,47-50].

### Aims

The first aim of the study is to determine the feasibility of the intervention, including its acceptability, and further refine intervention materials and study procedures (recruitment, enrollment, intervention, retention, and data collection). The second aim of study is to test the effects of the intervention on maternal outcomes from baseline at 22–36 weeks pregnant (Time 1) to 6 weeks postpartum (Time 2), 4 months postpartum and completion of Phase I (Time 3), 7 months postpartum and completion of Phase II (Time 4), and 10 months postpartum, after 3 months on their own (Time 5). The primary maternal outcome is a decrease in fasting blood glucose and weight from baseline to 10 months postpartum. Secondary maternal outcomes include a decrease in glucose levels from the oral glucose tolerance test, insulin levels, homeostatic model assessment of insulin resistance (HOMA-IR), glycated hemoglobin A1C (A1C), lipid panel, blood pressure, and adiposity, as well as improvement in health behaviors, eating, exercise and breastfeeding self-efficacy from baseline to 10 months postpartum. The third aim of the study is to quantify the effects of the intervention on infant feeding and growth outcomes (weight status [weight-for-length]) and breastfeeding (weeks until stopped breastfeeding, weeks exclusively breastfed, and intensity of breastfeeding) from birth to 10 months postpartum.

## Methods

### Design

The study will use a two-group, randomized, repeated measures design to test the feasibility of the adapted NEST intervention for women diagnosed with GDM during their current pregnancy. See Figure 1. An experimental group of women (n = 50) will receive a two-phased intervention with follow-up. In Phase I (Intensive Intervention), interventionists will meet with women in small groups for 14 sessions. The initial session, during pregnancy, will focus on the benefits of and strategies to sustain breastfeeding. The remaining sessions, on diabetes, nutrition and exercise education, coping skills training, exercise, and a home-based exercise program, will start when they are about 6 weeks postpartum. Participants will also receive weekly educational and motivational text messages. In Phase II (Continued Support), interventionists will hold monthly meetings with the women for 3 months to discuss problems related to breastfeeding, nutrition and exercise, and to provide feedback and support. Data will be collected at baseline at 22–36 weeks pregnant (Time 1), to 6 weeks postpartum (Time 2), 4 months postpartum and completion of Phase I (Time 3), 7 months postpartum and completion of Phase II (Time 4), and 10 months postpartum, after 3 months on their own (Time 5). Time 3 and Time 4 data collections will determine the magnitude of intervention effects after Phase I and Phase II respectively; Time 5 will determine whether women have maintained their new skills. Three to 6 months after completion is a standard length of time for follow-up in weight management studies [52].

**Figure 1 F1:**
[figure not shown]
Randomization for the trial.

A wait-list control group (n = 50) will receive usual care and will have the same data collection schedule as the experimental group (Time 1-Time 5). After they complete the Time 5 data collection, they will be offered sessions 2–14 only.

### Settings

The study is being conducted in partnership with the University of North Carolina at Chapel Hill (UNC-CH) Schools of Nursing and Medicine and two clinical sites, Rex Healthcare and WakeMed. Our team has had a longstanding relationship with both sites. A local church near Rex Healthcare and a community center near WakeMed are being utilized for enrollment, data collection and delivery of the intervention. Women will be enrolled during four enrollment periods. After each of the four enrollment periods, the sites will be randomized to the experimental or wait-list control group. Women will be told their group assignment by phone.

### Power analysis

Eighty women are expected to complete the study; 40 per group. We will induct 100 women to take into account a 20% attrition rate seen in our previous studies [37-39,53]. While individually randomizing women to either the experimental or wait-list control group would be ideal, this is not feasible in our settings because of the limited number of women with GDM available in each site during any given enrollment period. Therefore, we have chosen a cluster-randomized approach. After a group of women is inducted, they will be randomly assigned to either the experimental group or the wait-list control group, to provide a balanced allocation in each site, yielding a random sequence of two experimental groups and two wait-list control groups for each site. This will provide two-group, longitudinal comparisons of complete data on 40 women per group, for analyses of changes in metabolic, clinical, weight, adiposity, health behaviors, and self-efficacy at up to four post-baseline time points. A cluster power calculation was performed with POWERLIB20 SAS/IML modules, which incorporate the methods described in Muller [54]. These methods calculate power for the general linear multivariate model, including repeated measures data, allowing adjustment for within-cluster correlation, which is expected to be small. We intend to determine effect size for each maternal and infant outcome addressed in Aims 2 and 3 in separate multivariate models. The study will be well powered to detect moderate to large effect sizes. An effect size of .67 SD at any post-baseline time point with this sample size will provide .80 power at the two-sided .05 significance level; an effect size of .8 SD increases the power to .92.

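### The stated power of .80 at .67 SD and .92 at .8 SD is not reached with 40 completers per arm once the test takes its degrees of freedom from the 8 randomised cohorts, unless baseline adjustment is credited

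*Protocol article*

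**What the plan says.** All from the protocol article.

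- **Sample size (Power analysis).** "Eighty women are expected to complete the study; 40 per group". The enrolled number follows from dropout: "We will induct 100 women to take into account a 20% attrition rate seen in our previous studies".
- **Unit of randomisation (Power analysis).** Randomising individual women is ruled out because too few are available per site and period. "Therefore, we have chosen a cluster-randomized approach", "yielding a random sequence of two experimental groups and two wait-list control groups for each site". Settings names two clinical sites and adds: "Women will be enrolled during four enrollment periods".
- **Power (Power analysis).** A cluster power calculation is reported, using software for the general linear multivariate model, "allowing adjustment for within-cluster correlation, which is expected to be small". Then: "An effect size of .67 SD at any post-baseline time point with this sample size will provide .80 power", two-sided at .05, and "an effect size of .8 SD increases the power to .92". The same paragraph calls the study well powered for moderate to large effects.
- **Analysis (Data analysis, Aims 2 and 3).** Linear mixed models adjusted for baseline, with a main effect of site, and with within-site and within-subject correlation. Cohort is not named.

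No ICC value, degrees of freedom, or baseline or repeated-measures correlation is given, and the SD in which .67 and .8 are measured is not defined.

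**The concern.** When 8 cohorts are randomised, variation between arms has to be judged against variation between cohorts. There are few cohorts, so the critical value is much larger than the one that applies to 80 independent women. This loss is separate from the variance inflation caused by the ICC, and a small ICC does not remove it. If the power calculation allowed for the inflation but kept degrees of freedom that count women, its result is too favourable.

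At stake is how the effect estimates are read. The Discussion presents them as the foundation for an efficacy study. A reader who trusts the power paragraph could take a null result as evidence against a moderate benefit, which this design has little chance of detecting.

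**Working it through.** **Inputs.** 40 completers per arm; 2 sites × 4 cohorts = 8 cohorts, 4 per arm; 80/8 = 10 completers per cohort; two-sided α = .05 (Power analysis, Settings). The 12–13 women per class given under Phase I agree with 100/8 = 12.5 enrolled. The ICC is not given; I assume 0, .01 and .05.

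**Formula.** Noncentral t with noncentrality d × √(20/DE). The 20 is 40/2, and DE = 1 + (10 − 1) × ICC. Here d is in SDs of the analysed measure, with no baseline credit.

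**Step 1: can the stated pair be reproduced?**

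| Basis | .67 SD | .8 SD |
|---|---|---|
| Stated | .80 | .92 |
| 40 v 40 women, no clustering, 78 df | .841 | .942 |
| 40 v 40, 78 df, ICC .0125 (DE = 1 + 9 × .0125 = 1.11) | .801 | .918 |
| 36 v 36 women, no clustering | .801 | .917 |
| 50 v 50 (no attrition), 6 df, ICC 0 | .796 | .912 |
| 40 v 40, 6 df, ICC 0 | .706 | .844 |

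Solving for DE on 78 df gives 1.116 from the first stated power and 1.103 from the second, so one setting explains both. On 6 df the DE would have to be .77–.79, and on 5 df .71–.73. Both are below 1, which a non-negative ICC cannot produce.

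**Step 2: power with cohort-level degrees of freedom.** Cohort means, 4 against 4, leave 8 − 2 = 6 df; a site term leaves 5. The critical t is 2.45 or 2.57, against 1.99 on 78 df. Example: at .67 SD and ICC 0 the noncentrality is .67 × √20 = 3.00, which gives .706 on 6 df and .671 on 5 df.

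| ICC (assumed) | DE | .67 SD (5–6 df) | .8 SD (5–6 df) | Effect for .80 power (6–5 df) |
|---|---|---|---|---|
| 0 | 1.00 | .67–.71 | .81–.84 | .75–.79 SD |
| .01 | 1.09 | .64–.67 | .78–.81 | .79–.82 SD |
| .05 | 1.45 | .52–.55 | .66–.70 | .91–.95 SD |

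A simulation of t-tests on cohort means (200,000 runs, 6 df, ICC 0) gave .707 and .843.

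**Step 3: a moderate effect.** The article does not define moderate; I take .5 SD.

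- 40 v 40 women, no clustering, 78 df: noncentrality .5 × √20 = 2.24, power .60.
- The setting that reproduces the stated pair (78 df, DE 1.11): .55.
- Cohort df: .44–.47 at ICC 0 and .33–.35 at ICC .05.

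**Step 4: credit for baseline adjustment.** If .67 and .8 are in unadjusted SDs, a baseline–outcome correlation r multiplies the noncentrality by 1/√(1 − r²).

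| r (assumed) | ICC (assumed) | .67 SD (5–6 df) | .8 SD (5–6 df) |
|---|---|---|---|
| .5 | 0 | .79–.82 | .91–.93 |
| .5 | .01 | .75–.79 | .88–.91 |
| .6 | .01 | .82–.85 | .92–.94 |
| .5 | .05 | .64–.67 | .78–.81 |

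The r that restores the stated pair is .46–.54 at ICC 0, .52–.59 at ICC .01 and .67–.72 at ICC .05.

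**The case against.** A reader might infer that the stated figures are plain individual-level power with clustering ignored. The documents do not support that. Individual-level power is .84 and .94, above what is stated, and the article says a cluster calculation was run. Some allowance for clustering appears to have been made.

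A reader might also infer that the calculation certainly counted women in its degrees of freedom. That is the simplest reading, since an ICC of about .0125 matches both figures. But it is back-solved from two rounded values, and other routes fit. One is 36 women per arm. Another uses cohort df, with all 100 women at ICC 0, but it sets aside the 20% attrition and the 40 per group on which the paragraph rests, and leaves no room for clustering: at ICC .01 it falls to .75 and .88.

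The strongest objection is baseline adjustment. It is planned, and the software handles repeated measures. If the effect sizes are in unadjusted SDs, a baseline correlation of about .5 at ICC 0, or about .5 to .6 at ICC .01, reaches the stated pair on cohort df. This stands: it is not true without condition that the design falls short even at ICC 0. But the article states no such correlation, and at ICC .05 about .7 would be needed.

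An article may also leave the ICC value to the full protocol, so its absence alone is no fault. The point concerns the power figures and the conclusion that the article prints. Finally, the first aim is feasibility and effect estimates are meant to guide a later study. That lowers the weight of the point without making the figures right.

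**Conclusion.** The point stands in a limited form. With 8 randomised cohorts of about 10 completers, a test on 5 or 6 df and no baseline credit, power at ICC 0 is about .67–.71 at .67 SD and .81–.84 at .8 SD. That is 9 to 13 points below the stated .80 and 8 to 11 points below the stated .92 (.80 − .71 and .80 − .67; .92 − .84 and .92 − .81). Any positive ICC widens the gap. This rests on cohort-level degrees of freedom, which follow from the randomisation scheme, and on d being in SDs of the analysed measure. It no longer holds if a sufficient baseline correlation is assumed, and the article gives none.

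That women were counted in the degrees of freedom is the likely explanation, not an established one. The claim of good power for moderate effects does not depend on it: at .5 SD, unadjusted power is .60 with no clustering and about .33–.47 on cohort df.

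This should be corrected, but with feasibility as the first aim it is not a defect that must be resolved before the trial can be relied on.

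**What to change.** Restate the power paragraph on between-cohort degrees of freedom (5 or 6). Name the ICC used, the SD in which effects are expressed and any baseline correlation credited, and show a range over plausible ICCs. Unadjusted, the effect detectable with .80 power is about .75–.79 SD at ICC 0 and .91–.95 SD at ICC .05; these ICCs are illustrations, and the sponsor should supply the values actually used. If a baseline correlation was credited, state it and its source. Remove the word moderate from the sentence that calls the study well powered.

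The cost is a rewording and, without baseline credit, less favourable figures. No change to enrolment, design or analysis is needed for this point.

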### Sample

The trial received ethical approval by the Institutional Review Board at The University of North Carolina at Chapel Hill, REX Healthcare and WakeMed. Women between 22–36 weeks of pregnancy who are diagnosed with GDM are eligible to enroll in the study. Inclusion criteria include a diagnosis of GDM during the current pregnancy by two or more 100 g Oral Glucose Tolerance Test values exceeding established thresholds (fasting 95, 1 h 180, 2 h 155, 3 h 140 mg/dL) [55]; age 18 years or older; a pre-pregnancy body mass index ≥ 25 kg/m^2^; ability to read and write in English; and willingness to consent for themselves and their infant. Health care providers will not be asked to give permission for women to join the study. Women will be excluded if they have an A1C ≥ 6.5 mg/dL indicating T2DM. The project manager contacted both sites and met with health care providers and staff to explain the study and distribute brochures. Any woman diagnosed with GDM who meets the inclusion criteria is given a brochure and asked to call the study number. The woman is then screened over the phone by the project manager. If the woman meets inclusion criteria and is interested in joining the study, an enrollment appointment is set up at one of the community centers at a convenient time for the woman to confirm eligibility and review the consent. The project manager confirms eligibility, explains the study, and answers all questions before asking the woman to consent for herself and her infant.

### Phase I intensive intervention

The Phase I classes are adapted from *Children and Parents Partnering Together to Manage their Weight*[56] and the feasibility study *Reducing the Risk of Chronic Disease: A Group- Based Weight Loss Program for Postpartum Mothers*[57] with additional sessions about 1) the importance of breastfeeding for metabolic control and infant health and 2) reinforcement of GDM reoccurrence with future pregnancies, and progression to prediabetes and T2DM [37-39,53]; and weekly educational and motivational text messages until women have completed their time in the study. Each 60-minute session will be delivered to a group of 12–13 women (Table 1). All women at both sites receive a GDM education class at the time of diagnosis by a certified diabetes educator. These existing classes are virtually identical. We have added two classes. We will deliver the first class during pregnancy, on the benefits of breastfeeding for metabolic control and for infant health. We will deliver the second class when women are 6 weeks postpartum to reinforce knowledge of recurrent GDM and progression to T2DM. To further support breastfeeding, our interventionists, who have experience in breastfeeding support, will contact experimental women weekly until they start classes (6 weeks postpartum) to inquire how breastfeeding is progressing and answer questions using a protocol we have developed with a consultant for our study, based on an effective pre- and post-natal breastfeeding intervention protocol [58]. We have a lactation consultant on the grant that will be available to assist with mother’s breastfeeding concerns. Also, at each site, registered dietitians will be available to discuss caloric needs with breastfeeding mothers in the experimental group [59].

**Table 1 T1:** Phase I intensive intervention

